### 2.8. Data Analysis

Data will be analyzed using Jamovi (Jamovi Project 2018, version 0.9.1.7, Sydney, Australia) and RStudio 3.15.0 software (PBC, Boston, MA, USA). Prior to data analysis, the Shapiro Wilk test and the Levene test will be performed to determine the normal distribution of the variables and the homogeneity of variance. Descriptive data will be reported as mean ± SD and range. All the data will be analyzed based on the intention-to-treat principle (last observation carried forward). If the sample is normally distributed, Student’s t-test will be calculated to compare variables before and after the intervention. For a variable to be considered as having a normal distribution, 95% of values will have to be within two standard deviations of the mean. If the sample is nonparametric, the U-Mann Whitney test will be used to compare variables before and after the intervention. The standardized mean differences (Cohen’s effect size) will be calculated together with the 95% confidence intervals [49]. The effect sizes (ES) will be calculated using Cohen’s d [49]. The relationship between variables will be assessed using the Pearson r correlation coefficient. If r is higher than 0.7, the determination coefficient (r^2^) will be used to determine the percentage of Y variation with regard to the X variation. Significance will be accepted at *p* ≤ 0.05.

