## 1. Introduction

It is known that training is essential for improving physical performance [1] and that optimizing training for performance improvement in athletes is an important area of research within exercise physiology and sports medicine [2,3,4]. In this regard, different training methods for performance improvement have been tried and tested, such as intensified training [2,5,6] and submaximal tests [7]. However, it is also recognized that using the same standardized training program for a group of athletes can provoke a wide range of reactions in terms of performance and physiological adaptations [8,9].

As stated by Schmitt, Willis, Fardel, Coulmy, and Millet [10], an important component of the interindividual variability in physiological responses to standardized training is related to the balance between the parasympathetic (PNS) and sympathetic (SNS) activity of the autonomic nervous system (ANS) [11,12]. Heart rate variability (HRV) is one of the indicators that allows the noninvasive study of autonomic nervous system activity in its sympathetic and parasympathetic branches [13,14]. HRV is understood as the variation in the time interval between two consecutive heartbeats. It is obtained by calculating the time interval that elapses between two consecutive R waves (i.e., RR interval fluctuation) on an electrocardiogram (ECG) [15]. The period between beats is not constant; consequently, high HRV values are associated with an efficient ANS, which promotes behavioral adaptation and cognitive flexibility during stress [16], whilst low HRV values are indicative of an inefficient ANS, resulting in maladaptive responses to stress and perceived threats [15]. Furthermore, HRV is considered to be an indicator of cardiovascular health level [17].

Given that the SNS is responsible for changes in heart rate (HR) due to stress, and that the HR is one of the first parameters used to control the body’s functional capacity [18], HRV analysis has been established as a useful method for assessing the heart’s ability to adapt to both endogenous and exogenous loads [19], and can be used for the individual assessment of responses to training loads. Indeed, in recent years, HRV has been used to analyze these imbalances between SNS and PNS in athletes [20] and to evaluate different aspects related to training [21] such as exercise intensity and duration [22], recovery and overtraining [23], training load [24] or psychophysiological profiles [25].

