### 2.5. Sample Size and Power

Calculations to establish the sample size will be performed using RStudio 3.15.0 software (PBC, Boston, USA). The significance level will be set at *p* ≤ 0.05. According to the mean standard deviation established for VO_2max_ in a previous study [31] (SD = 1.5 mL/kg/min) and an estimated error (*d*) of 1.1, a valid sample size providing a 95% confidence interval (CI) in each group will be 7 (*n* = *CI*^2^ × *d*^2^/*SD*^2^). Thus, a final sample size of 7 for each group will provide a power of 93% if between and within a variance of 2.

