### 2.7. Allocation and Blinding

A block randomization method will be used to allocate participants to the groups, which will contain equal sample sizes. The block size will be determined by the data monitoring committee according to the statistical power provided. Blocks will be chosen randomly by tossing a coin to determine the participants’ assignment into the groups. This procedure will be carried out by the data monitoring committee. The athletes and the data monitoring committee will be blinded to the exercise group assignment.

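### Levene's test decides nothing and only Student's t-test is named; the error-rate cost is small at 7 v 7 and becomes material only if the analysed arms end up unequal

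*Protocol article*

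**What the plan says.** Section 2.8 (Data Analysis) of the protocol article plans two preliminary checks: "the Shapiro Wilk test and the Levene test will be performed to determine the normal distribution of the variables and the homogeneity of variance". The choice of test then rests on the first check only: "If the sample is normally distributed, Student’s t-test will be calculated to compare variables before and after the intervention". The alternative is "If the sample is nonparametric, the U-Mann Whitney test will be used to compare variables before and after the intervention". No sentence says what follows if Levene's test rejects, and no unequal-variance method is named. The threshold is "Significance will be accepted at *p* ≤ 0.05"; sidedness is not stated.

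Three other sections bear on the arm sizes:
- Section 2.5 plans 7 athletes per group: "a final sample size of 7 for each group will provide a power of 93" per cent. Section 2.7 describes a method to "allocate participants to the groups, which will contain equal sample sizes".
- Section 2.8 applies intention-to-treat with last observation carried forward.
- Section 2.2 lists completing fewer than 90% of workouts as an exclusion criterion, and section 2.4 places the pretest in week 5, after the four-week preparation period.

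**The concern.** A variance check that changes nothing leaves two possibilities if it rejects. Either the pooled-variance test is used anyway, or someone chooses another test after seeing the data. Mann-Whitney is reserved for non-normal data and is not a remedy for unequal variances.

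Objective (ii) compares the two arms, and section 2.8 names no other test for it. If Student's t is that test, its standard error uses a pooled SD. Were the SDs of the two arms to differ, the true error rate would no longer be exactly 5%. The direction and size of the departure depend on the arm sizes.

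**Working it through.** **Inputs.** From the article: 7 per arm (2.5), equal arms (2.7), significance at 0.05 (2.8). Assumed here: two-sided testing, normal data, between-arm SD ratios of 1 to 4 with 10 as an extreme, and 7 v 5 as an example of unequal analysed arms. The article gives no SD by arm (2.5 uses one value, 1.5 mL/kg/min) and no dropout rate.

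**The plan's own figure.** The 93% power is reproduced as a two-group comparison with a between-to-within variance ratio of 2:
- Noncentrality = (2 − 1) × 7 × 2 = 14 on 1 and 12 df, giving 92.9%.
- Equivalently, a standardised difference of 2: 2 × √(7/2) = 3.74, and 3.74² = 14.

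So the stated power corresponds to a between-arm test with a common within-arm variance, which is the setting in which this point arises.

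**Why arm size matters.** Compare the variance of the mean difference that Student's test estimates on average, [((n1−1)σ1² + (n2−1)σ2²)/(n1+n2−2)] × (1/n1 + 1/n2), with the true variance σ1²/n1 + σ2²/n2. Take SDs of 1 and 2:
- 7 v 7: pooled variance (6×1 + 6×4)/12 = 2.5; × 2/7 = 0.714. True: 1/7 + 4/7 = 0.714. Ratio 1.00.
- 7 v 5, smaller arm more variable: (6×1 + 4×4)/10 = 2.2; × (1/7 + 1/5) = 0.754. True: 1/7 + 4/5 = 0.943. Ratio 0.80, so the test is too liberal.
- 7 v 5, larger arm more variable: (6×4 + 4×1)/10 = 2.8; × 0.343 = 0.960. True: 4/7 + 1/5 = 0.771. Ratio 1.24, so it is too conservative.

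With equal arms the estimated variance is right on average. Only the degrees of freedom are overstated.

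**Simulated type I error** (normal data under the null, 400,000 runs per setting, nominal 5%):

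| Arms | SD ratio | Student | Welch |
|---|---|---|---|
| 7 v 7 | 1 | 5.0% | 4.7% |
| 7 v 7 | 1.5 | 5.2% | 4.8% |
| 7 v 7 | 2 | 5.6% | 4.9% |
| 7 v 7 | 3 | 6.2% | 5.1% |
| 7 v 7 | 4 | 6.6% | 5.2% |
| 7 v 7 | 10 | 7.2% | 5.1% |
| 7 v 5, smaller arm more variable | 2 | 8.4% | 5.4% |
| 7 v 5, smaller arm more variable | 3 | 10.5% | 5.4% |
| 7 v 5, larger arm more variable | 2 | 3.7% | 4.8% |
| 7 v 5, larger arm more variable | 3 | 3.6% | 5.0% |

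Repeat simulations agree to within about 0.1 point; the 10.5% entry came out at 10.6%.

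**Ceiling at 7 v 7.** As the SD ratio grows without limit, the statistic tends to a t variable on 6 df but is still compared with the 12-df critical value 2.179. P(|t6| > 2.179) = 7.2%.

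**Would acting on Levene's test help?** At 7 v 7 it detects an SD ratio of 2 in 29% of trials and a ratio of 3 in 55%. Letting it choose between Student and Welch gives 5.3% and 5.7%, against 5.6% and 6.2% for Student alone. It adds little.

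**Can the analysed arms become unequal?** Carrying the last observation forward keeps an athlete in the analysis only if an outcome value exists. An athlete lost before the week-5 pretest has no treadmill value to carry. Separately, applying the section 2.2 attendance criterion would remove athletes after allocation, which sits uneasily with intention-to-treat in section 2.8. The article therefore leaves unequal arms open, without saying how likely they are.

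**The case against.** Five arguments count against making more of this.

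1. *The planned design is balanced.* At 7 v 7 Student's test is robust, and carrying observations forward preserves the balance for athletes lost after the pretest. This stands. A reader might infer that the error rate drifts appreciably in the trial as planned. It does not: the excess is 0.6 points at a twofold SD ratio and 1.2 points at a threefold one.

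2. *Unequal spread is not something the plan predicts.* The introduction says that "using the same standardized training program for a group of athletes can provoke a wide range of reactions in terms of performance", and a reader might infer that the authors expect TRAD-G to be the more variable arm. The sentence concerns athletes on one programme. It says nothing about spread under HRV guidance, and HRV-G athletes will themselves receive differing amounts of hard training. Different spread is plausible, but neither its existence nor its direction is stated.

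3. *The t-test is worded as a pre-to-post comparison.* A paired test within an arm needs no equal-variance assumption. This also stands as a reading of the sentence. The between-arm use is inferred from objective (ii), from planning Levene's test at all, and from the fallback being an independent-samples test. A reader should not take the article to say expressly that Student's t is used between arms after Levene's test rejects.

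4. *Such detail is often left to the analysis plan.* True in general, and a reason to keep the point small. But section 2.8 does set out the checks, the tests and a selection rule, and that rule ignores one of the checks.

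5. *Welch does not secure the error rate.* With one club per arm, analysing athletes as independent matters more. At an assumed intraclass correlation of 0.05, the inflation factor √[(1 + 6×0.05)/(1 − 0.05)] = 1.17 takes the same t-test to about 8.7%. That is a separate issue, which this change leaves untouched.

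**Conclusion.** The point holds in a limited form. Levene's test is planned without consequence, and the one test named for normal data assumes equal variances if it serves as the between-arm test. In the planned 7 v 7 comparison the cost is small and bounded at about 7.2% for normal data. It is material only if the analysed arms are unequal and the SDs differ substantially: roughly 8.4% to 10.6%, or about 3.7%, at 7 v 5, depending on which arm is more variable. Those figures rest on assumed SD ratios of 2 to 3, an assumed loss of two athletes from one arm, normality and two-sided testing. The documents supply neither the ratios nor the loss. This is a minor improvement, not a flaw that threatens the conclusion.

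**What to change.** In section 2.8, name Welch's t-test and its confidence interval for the HRV-G versus TRAD-G comparison of normally distributed variables, and delete Levene's test. Making the choice of Welch conditional on Levene's result is not recommended, given its low power at this size.

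The cost is one sentence and a little power if the variances are truly equal. For a 2-SD difference, power falls from 92.9% to about 92.4% at 7 v 7 (0.5 points) and from 86.7% to about 84.2% at 7 v 5 (2.5 points). In return, type I error stays within about 4.7% to 5.4% in the settings above.

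Reconciling the 90%-of-workouts criterion in section 2.2 with intention-to-treat in section 2.8 would close one route to unequal arms. Clustering by club needs its own treatment.

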### 2.4. Outcomes

The primary outcome of this study will be the maximal oxygen uptake (VO_2max_) obtained in an incremental treadmill test. The secondary outcomes will be: the maximal speed in m/s, maximal heart rate, respiratory exchange ratio, ventilatory thresholds (VT1 and VT2) and their derived speed, heart rate, respiratory exchange ratio and VO_2_ obtained in the incremental treadmill test. Other measurements considered as secondary outcomes will be: the time, speed, heart rate, rating of perceived exertion (RPE) and lactate in the 3000 m running test. Body composition and rMSSD will be considered as other variables.

Measurements will be taken before and after the training period, which will correspond to weeks 5 (pretest) and 12 (post-test). Over the assessment weeks, care will be taken that participants do not carry out any high-intensity training sessions. Each assessment week will consist of two testing sessions with a 48-h recovery period. The first testing session will include maximal graded exercise test and body composition measurements. In the second testing session, athletes will perform a 3000 m running test. The rMSSD will be measured daily, as explained in the intervention section.

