## 3. Discussion

This protocol describes the rationale, design, and methods of an HRV-guided training design for professional endurance athletes. It will allow accomplishment of a randomized controlled intervention to determine changes in the performance of high-level athletes after following an HRV-guided or a traditional training period, Moreover, the differences in the athletes’ performance after following both training protocols will be determined. To design this protocol with professional endurance athletes, the guidelines described in Kiviniemi et al. [34] have been followed. This procedure has also been adapted in other professional sports such as cycling [24,50] and skiing [10], as well as to amateur endurance athletes [28,29,30,31].

This is the first time that this kind of protocol will be applied in endurance elite athletes. After its implementation, we expect that both high-level athletes groups (HRV-G and TRAD-G) improve: (i) VO_2max_ and other secondary outcomes measured in the treadmill test (the maximal speed in m/s, maximal heart rate, respiratory exchange ratio, or ventilatory thresholds), (ii) the time, speed, heart rate, rating of perceived exertion (RPE) and lactate in the 3000 m running test. Additionally, HRV-G will be better regarding performance results than the TRAD-G. These findings will suggest that training guidance balancing the sympathetic and parasympathetic autonomic nervous system leads to greater athletic performance in endurance athletes compared to standardized prescribed training. This is relevant for training optimization and for minimizing overuse and reducing injury risk.

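### With only a pretest and a post-test, last observation carried forward records a missing VO2max post-test as zero change, which biases the between-arm contrast when post-tests are missing, in either direction if dropout is unequal

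*Protocol article*

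**What the plan says.** Section 2.8 (Data Analysis) fixes one missing-data rule for everything: "All the data will be analyzed based on the intention-to-treat principle (last observation carried forward". It names no alternative and no sensitivity analysis.

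Section 2.4 (Outcomes) sets the primary outcome, "The primary outcome of this study will be the maximal oxygen uptake", and its timing: "Measurements will be taken before and after the training period, which will correspond to weeks 5 (pretest) and 12 (post-test". The only measure taken between those weeks is heart rate variability: "The rMSSD will be measured daily, as explained in the intervention section".

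The Discussion states what is expected: "we expect that both high-level athletes groups (HRV-G and TRAD-G) improve", and then "Additionally, HRV-G will be better regarding performance results than the TRAD-G".

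Section 2.5 plans 7 athletes per group and states no allowance for dropout. Section 2.2 lists, as exclusion criterion (v), completing less than 90% of the workouts during the intervention.

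**The concern.** Carrying the last observation forward presumes intermediate measurements. VO2max has none, so the rule becomes baseline carried forward: an athlete with a pretest and no post-test enters the analysis with a change of exactly zero. The same holds for the other treadmill, 3000 m and body-composition outcomes measured only before and after training. It does not hold for daily rMSSD, and a missing pretest leaves nothing to carry.

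Zero is not a neutral value here, because the protocol expects improvement in both arms and does not argue that athletes who leave would stay unchanged. The imputed zeros are also analysed as if they had been observed. With 7 per arm, one athlete is 1/7, or 14%, of the group. The size of the primary contrast, and possibly its sign, could then depend on who misses the week 12 test.

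**Working it through.** **Inputs from the protocol.** Two VO2max assessments (section 2.4); 7 per group, SD 1.5 and d = 1.1 (section 2.5); significance at 0.05 (sections 2.5 and 2.8, taken as two-sided); improvement expected in both arms (Discussion).

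**Assumptions.** Mean gains of 1, 2 or 3 mL/kg/min; 0, 1 or 2 missing post-tests per arm; an SD of 1.5 for change; 1.1 as an illustrative true difference; athletes treated as independent; post-tests missing at random. None of these is given in the protocol in that role.

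**The plan's own figure.** No figure is given for the effect of the carry-forward rule. The planned 7 per group reproduces as 1.96² × 1.5² / 1.1² = 7.14. (The formula as printed has the ratio inverted and gives 1.96² × 1.1² / 1.5² = 2.07; that is a separate matter.)

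**Bias formula.** Let gH and gT be the true mean gains in HRV-G and TRAD-G, and mH and mT the numbers of missing post-tests. Each missing athlete contributes zero, so

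expected contrast = (1 − mH/7) × gH − (1 − mT/7) × gT

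bias = −(mH/7) × gH + (mT/7) × gT

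**No missing post-tests.** mH = mT = 0, so the bias is 0.

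**Equal dropout.** With mH = mT = m the bias is −(m/7) × (gH − gT). For a true difference of 1.1:
- one per arm: 6/7 × 1.1 = 0.94 (−14%)
- two per arm: 5/7 × 1.1 = 0.79 (−29%)

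If the gains are equal, this bias is zero.

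**Unequal dropout, no true difference.** Two missing in one arm gives a spurious difference of 2/7 × g in favour of the other arm. Rejection rates come from simulating 100,000 trials with a between-arm t-test on change.

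| Common gain | Spurious difference | Type I error, carry-forward | Type I error, observed data |
|---|---|---|---|
| 1 | 0.29 | about 6% | about 5% |
| 2 | 0.57 | about 9% | about 5% |
| 3 | 0.86 | about 10% | about 5% |

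With one missing in one arm and a common gain of 2, the estimate moves by 1/7 × 2 = 0.29, and type I error stays at about 5.1%.

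**Unequal dropout, true difference 1.1** (gH = gT + 1.1):

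| TRAD-G gain | Two missing in HRV-G | Two missing in TRAD-G |
|---|---|---|
| 1 | 5/7 × 2.1 − 1 = 0.50 | 2.1 − 5/7 × 1 = 1.39 |
| 2 | 5/7 × 3.1 − 2 = 0.21 | 3.1 − 5/7 × 2 = 1.67 |
| 3 | 5/7 × 4.1 − 3 = −0.07 | 4.1 − 5/7 × 3 = 1.96 |

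The observed-data analysis averaged 1.09 to 1.11 in every simulated scenario with a true difference of 1.1.

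**Effect on spread.** Zeros placed among positive changes also distort the within-arm SD. With gains of 3.1 and 2.0 and two missing per arm, power is about 3% under carry-forward and about 18% on observed data.

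**The case against.** Several points on the other side stand.

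- **Joint improvement alone does no harm.** A reader might infer that the contrast is biased simply because both arms are expected to improve. It is not. With equal gains of 2.0 and two missing per arm, the bias is zero and the test rejects in only about 1% of trials. Under equal dropout the shrinkage comes from the difference in gains; the common gain matters when dropout is unequal.
- **1.1 is not a planned difference.** Section 2.5 gives "SD = 1.5 mL/kg/min) and an estimated error (*d*) of 1.1", so 1.1 enters as an estimated error in a precision formula. Describing the bias as a share of a target effect would go beyond the text.
- **One athlete does not create false positives.** In the scenario above, one missing athlete shifts the estimate but barely moves the error rate.
- **The error rates depend on the test.** Section 2.8 says only that a t-test compares values before and after the intervention. If the arms were compared on post-test values, with an assumed between-athlete SD of 3 to 5 and the same dropout, type I error would be about 5.4% to 5.7%.
- **The rule may seldom apply.** Section 2.6 secures a commitment to attend both tests. If criterion (v) removes athletes from the analysis, many likely dropouts would never be imputed. That reading conflicts with intention-to-treat, however, and an adherent athlete can still miss the post-test.

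Two general defences do not succeed. The rule cannot be treated as a detail left to an unseen analysis plan, because the article names it. Nor is it reliably conservative: with unequal dropout it can turn a true 1.1 into 1.67.

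**Conclusion.** The concern holds in conditional form. For an athlete with a pretest and no post-test, the stated rule imputes zero change in VO2max, against the protocol's own expectation. If post-tests are complete, nothing is lost. If they are missing equally, a true difference shrinks by the missing share: 14% with one of seven per arm, 29% with two. If they are missing unequally, the contrast can move towards either arm. With two missing in one arm and assumed gains of 1 to 3 mL/kg/min, the spurious difference is 0.29 to 0.86, with type I error of about 6% to 10% for a t-test on change.

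The direction of bias follows from the protocol once the dropout pattern and gains are specified. The sizes rest on assumed gains, missing counts and SD of change, and the error rates also on the assumed test. The documents do not support saying that the VO2max contrast will be biased, or that HRV-G in particular would benefit. The rule should be changed, but this point does not by itself invalidate the design.

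**What to change.** In section 2.8, delete last observation carried forward as the primary missing-data method. In its place:

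1. Analyse all randomised athletes by assigned group, using a pretest-adjusted analysis of the observed post-tests: ANCOVA, or the equivalent constrained longitudinal model, which also keeps the pretests of athletes without a post-test.
2. State the assumption this needs, that post-tests are missing at random given the pretest and group. It could fail, for example if athletes who respond poorly are the ones who leave.
3. Add a sensitivity analysis for that assumption: multiple imputation or a best-case/worst-case range.
4. Reconcile exclusion criterion (v) in section 2.2 with the intention-to-treat statement in section 2.8, so that it is clear whether athletes below 90% of workouts remain in the primary analysis.

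The cost is analysis wording only; no visit, measurement or sample-size change is required. The estimate rests on fewer values, but the interval need not be wider, because imputed zeros can inflate the SD. In a simulation with gains of 3.1 and 2.0 and one missing per arm, the mean 95% half-width was 1.88 on observed data and 1.96 under carry-forward.

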Until just a few years ago, conducting research of this type, involving daily HRV measurements on each athlete and then adapting training based on these data, was only possible with the collaboration of high-cost laboratories. This study tests the use of noninvasive, commercial, low-cost and publicly accessible technology to evaluate the physiological responses obtained by adapting training to HRV.

Based on everything described above, we hypothesize that HRV-guided training will: (i) improve functional performance in high-level athletes and (ii) produce better performance results than a traditional training method. The objectives of the proposed protocol are: (i) to determine changes in the performance of high-level athletes after following an HRV-guided or a traditional training period, and (ii) to determine differences in the athletes’ performance after following both training protocols.

This will be a 12-week cluster-randomized controlled trial protocol in which professional athletes are assigned to either an HRV-based training group (HRV-G) or a traditional-based training group (TRAD-G). A block randomization method will be chosen to randomly assign participants to interventions in equally sized sample groups. This protocol has been designed following the Standard Protocol Items: Recommendations for Interventional Trials (SPIRIT) Statement [32]. To describe the intervention, the TIDieR (Template for Intervention Description and Replication) checklist by Hoffmann et al. [33] has been used.

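### The analysis section gives both tests a before-and-after contrast and names no HRV-G versus TRAD-G comparison, so on either reading one of the two objectives has no test

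*Protocol article*

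**What the plan says.** The Introduction of the protocol article sets a between-arm hypothesis, that HRV-guided training will "produce better performance results than a traditional training method", and a between-arm objective, "to determine differences in the athletes’ performance after following both training protocols". Its other hypothesis and objective, both numbered (i), concern change after each kind of training. The Discussion expects both groups to improve and adds: "Additionally, HRV-G will be better regarding performance results than the TRAD-G".

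Section 2.4 makes VO2max on the treadmill test the primary outcome and places the measurements before and after the training period, "which will correspond to weeks 5 (pretest) and 12 (post-test". Every athlete therefore has a pretest value.

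Section 2.8 names two tests of effect. If the data are normal, a Student's "t-test will be calculated to compare variables before and after the intervention". If not, "the U-Mann Whitney test will be used to compare variables before and after the intervention". It also plans a Levene test, Pearson correlations and an effect size: "The standardized mean differences (Cohen’s effect size) will be calculated together with the 95% confidence intervals". The section does not mention either arm, a group or group-by-time term, a change score or a role for the pretest. It does not say whether Cohen's d is within or between arms.

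**The concern.** The contrast that section 2.8 attaches to both tests is not the contrast that hypothesis (ii) needs. Taken literally, the section yields one p-value per arm, and the only route from those to a superiority statement is to note that one arm was significant and the other was not. That is not a test of the difference. With 7 athletes per arm, two arms with the same true gain will often fall on opposite sides of 0.05.

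The wording can also be read as a comparison of the arms at pretest and again at post-test. Then change within each protocol is not tested, and the post-test comparison takes no account of where each athlete started. At stake are whether the main hypothesis is tested at all, and how precisely.

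**Working it through.** **1. The plan's own figures (section 2.5).** These show which comparison the trial was sized for.
- Sample size: 1.96² × 1.5² / 1.1² = 7.14, which gives 7. As printed, with the ratio the other way up, the formula gives 1.96² × 1.1² / 1.5² = 2.07. This is a precision formula and tests nothing.
- Power: for a two-group one-way ANOVA with n = 7 per group, the noncentrality is (2 − 1) × 7 × (between variance / within variance) on F(1, 12). A variance ratio of 2 gives 0.929, which matches the stated 93%. Taking both variances as 2 gives 0.681, which does not.

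So the 93% is recovered as a between-arm power. On that reconstruction, the trial is powered for a comparison that section 2.8 does not name.

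**2. Literal reading: a test within each arm.** Inputs are n = 7 per arm, two-sided 0.05 (the article does not state sidedness), independent arms and the same true standardised change dz (mean change divided by SD of change) in both. The power p of one paired t-test comes from the noncentral t on 6 df with noncentrality dz × √7. HRV-G alone is significant with probability p(1 − p); exactly one arm is significant with probability 2p(1 − p).

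| dz | p | HRV-G alone | exactly one arm |
|---|---|---|---|
| 0.50 | 0.201 | 16% | 32% |
| 0.73 | 0.37 | 23% | 47% |
| 0.84 | 0.463 | 25% | 50% |
| 1.00 | 0.600 | 24% | 48% |
| 1.33 | 0.833 | 14% | 28% |
| 1.50 | 0.908 | 8% | 17% |
| 2.00 | 0.991 | 1% | 2% |

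A direct two-sided 5% test of the difference would wrongly favour HRV-G in 2.5% of trials. The row at 0.73 is 1.1/1.5. Section 2.5 calls these figures an estimated error and an SD for VO2max, not a mean change and an SD of change, so that row is only one point in an assumed range.

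Mann-Whitney U also requires independent samples. Pretest and post-test values from the same athletes are paired, so under this reading the nonparametric branch is wrong as well.

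**3. Other reading: arm against arm at each time point.** The post-test comparison has residual variance σ². Adjusting for the pretest leaves σ²(1 − ρ²), where ρ is the pre-post correlation. The article gives no ρ; 0.7 to 0.9 is assumed.
- ρ = 0.7: 0.7² = 0.49, so 49% of the variance is removed.
- ρ = 0.9: 0.9² = 0.81, so 81% is removed.

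For the 95% CI half-width of the post-test difference at 7 + 7, take 1.5 as the SD of VO2max. Unadjusted: 2.179 × 1.5 × √(2/7) = 1.75 mL/kg/min. With ANCOVA it is about 1.3 (ρ = 0.7) or 0.8 (ρ = 0.9). If 1.5 is instead the SD of change, the post-test SD is 1.5/√(2(1 − ρ)), or 1.94 and 3.35. The unadjusted half-widths become 2.26 and 3.91, against about 1.7 and 1.8 with ANCOVA.

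Under this reading nothing tests change within an arm, so objective (i) is unserved.

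**The case against.** The strongest reply is that the authors meant to compare the arms and worded it loosely. Mann-Whitney U is for independent samples, a Levene test has no role in a paired analysis, the t-test is never called paired, and the stated power reproduces as a between-arm figure. Cohen's d with its interval may also be a between-arm estimate. This stands to the extent that a reader should not infer that the trial will certainly judge superiority from two within-arm p-values; the text leaves the reading open. It does not rescue the section, because under the arm-against-arm reading objective (i) loses its test and the pretest goes unused.

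A reader might also infer that the false-positive rate is far above 5% whenever both arms improve. That is not general. HRV-G-alone significance falls to 8% at a standardised change of 1.5 and 1% at 2.0, because both arms are then nearly always significant. Nor does ignoring the pretest always discard most of the precision: at a correlation of 0.7 it is about half the variance.

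Finally, the choice of covariate is commonly left to a statistical analysis plan, and a two-sample test on change scores is a reasonable alternative. In simulation with a true difference of 0.73 SD, change scores had power of 24%, 36% and 80% at correlations of 0.5, 0.7 and 0.9, against 27%, 39% and 78% for ANCOVA. So leaving out ANCOVA is not in itself the fault. The fault is that the section does state a contrast for its tests, and the stated contrast does not answer objective (ii).

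**Conclusion.** The point holds. Section 2.8 specifies what its tests compare, and on neither reading are both objectives tested. On the literal reading the superiority hypothesis has no test. The informal substitute would wrongly single out HRV-G in about 14% to 25% of trials with equal true gains, for assumed standardised changes of 0.5 to 1.33, and less often for larger changes. On the other reading objective (i) has no test, and 49% to 81% of the removable-by-pretest variance is left in the primary comparison at assumed correlations of 0.7 to 0.9. These figures assume two-sided 0.05, 7 athletes per arm and athletes who can be treated as independent.

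That last assumption is fragile. Sections 2.1 and 2.6 refer to two institutions and to a club being randomised. If each arm is one club, no athlete-level analysis, including the one proposed below, can separate the effect of training from that of club. A reader should not infer that naming the right contrast would by itself support a superiority claim.

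**What to change.** In section 2.8:
- Make the primary analysis a between-arm comparison of post-test VO2max with pretest VO2max as covariate (ANCOVA). Report the adjusted HRV-G minus TRAD-G difference in mL/kg/min with its 95% CI.
- Base any between-arm statement on that estimate, not on within-arm p-values.
- For objective (i), report the change within each arm with its CI and a paired test, using Wilcoxon signed-rank in place of Mann-Whitney U if a nonparametric test is needed.
- If each arm is a single club, state that the adjusted difference cannot separate the training effect from the club effect.

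The cost is one paragraph and one residual degree of freedom (14 − 2 = 12 falls to 14 − 3 = 11). No further data are needed, because the pretest is already collected.
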